The feasibility and acceptability of the study will be assessed in line with the MRC guidance on Developing and evaluating complex interventions (Craig 2019). These outcomes will assess participants that have completed or take part in the intervention part of the study and will be the following:

1. Adherence- interventions will run over 8 weeks. The completion of 4 weeks for mindfulness and 30min of home-based exercise weekly for two thirds (67%) of the duration of the trial will be regarded as adherence to the program. These levels of adherence are based on previous studies that have used the same levels (Mock *et al.* 2005; Pinto *et al.* 2005; Kim *et al.* 2019; Park *et al.* 2020) This will be assessed through the electronic diaries/logs that participants will be encouraged to complete along with the website/app data information- on frequency and duration of participant engagement with each session.
2. Attrition-We will estimate, following a review of web-based mindfulness intervention studies that the attrition rate will be approximately 20% with 10% to 15% of missing data (Carlson *et al.* 2019; Subnis *et al.* 2020).
3. Time to recruit, recruitment and retention rates, reasons for non-participation and acceptability of data collection. Time to recruit, recruitment and retention rates will be gathered through administrative data during (pre)screening, enrolment, allocation and follow-up. Reasons for non-participation, intervention/study dropouts will be collected when possible. Acceptability of data collection will be retrieved through missing data within questionnaires.
4. Acceptability of the programme will be assessed using focus groups this will include participants experience on the virtual delivery and data collection along with their experience and reflections on the exercise and mindfulness components of the intervention it will be achieved in the following way:

Design

Qualitative data collection utilising online focus groups will be facilitated via the Microsoft Teams (MS Teams) interface. This format for focus group has advantages including less dropout, more relaxed participants resulting in better communication, a more diverse group as able to include participants that are further away and cost-effective (Halliday *et al.* 2021)

Participants

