Participants will be encouraged to increase the intensity of the exercise dependent on the reported perceived experience of exertion using the Borg scale. This scale has a maximum level of 20 with 6 meaning no effort and 20 maximal effort (Thorsen *et al.* 2005) Participants will be asked to maintain exercise intensity to a level of 13 to 15 which is comparable to slightly strenuous and strenuous. Information on this scale along with exercise information will be available on the mobile app (appendix a). This will be supplemented with either audio or video demonstrations of individual strength exercises and explanations of walking intensity (appendix a). Participants will be asked to keep exercise logs recording the time and intensity of the walk using the Borg scale along with the number of sets and repetitions of strength exercises performed (appendix a). Participants will be contacted by the researcher every week at a time agreed between participant and researcher, this weekly contact will be to assess if there are any issues and set goals for the following week. Participants will be given the contact details of the researcher if they have any questions or concerns regarding the intervention. Participants will be educated as to what side effects to expect and any that they should be reporting to the research team. The researcher, [name], has completed a strength and conditioning course to enable her to safely educate and discuss goals with participants. A distress protocol is in place and will be followed if required. (appendix b). Alongside this guidance on managing participants that may have bone metastasis will be taken form the Macmillan guide ‘Physical Activity for People with Metastatic Bone Disease’ (Macmillan ). A risk assessment has been performed and interventions to reduce risk have been implemented.

Mindfulness

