| Log of exercise and walking activity. | Manual log with drop down of walking and minutes. For strength a drop down of type of exercise and sets and reps. Borg scale so participants can slide across at how much effort the exercise activity exerted. |

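### Exercise adherence rests on a manual log that women are only encouraged or asked to fill in, and the weekly contact is not used to tell an unlogged week from an unexercised one

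*Protocol*

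**What the plan says.** Protocol, Primary Outcome, item 1 (repeated under Statistical Model) sets the exercise criterion: "30min of home-based exercise weekly for two thirds (67%) of the duration of the trial will be regarded as adherence to the program". The programme length is fixed in the same item: "interventions will run over 8 weeks". Two data sources are named. The first is the diaries or logs: "This will be assessed through the electronic diaries/logs that participants will be encouraged to complete along with the website/app data". The second is the website or app information "on frequency and duration of participant engagement with each session".

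The Exercise Intervention description is slightly firmer about the log: "Participants will be asked to keep exercise logs recording the time and intensity of the walk using the Borg scale". Appendix a shows how exercise gets into the app in each week's table: "Manual log with drop down of walking and minutes". Strength work is entered there as exercise type, sets and repetitions. No sensor or automatic capture is described.

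The same description provides a regular contact: "Participants will be contacted by the researcher every week at a time agreed between participant and researcher". Its purpose is stated: "this weekly contact will be to assess if there are any issues and set goals for the following week". The Mindfulness description has the same weekly contact, so it takes place in both arms.

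The only other exercise measure is the short-form physical activity questionnaire. It covers the last seven days and, according to Appendix 14, is given at baseline and close-out only.

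**The concern.** The exercise criterion counts weeks, so every week needs a known status. The only source that can supply weekly minutes is the participant's own entry, and completing it is not required. App engagement data do not measure home walking or strength work. The activity questionnaire looks back one week from two time points, so it cannot fill the weeks in between. The weekly contact could supply the missing status, but its stated purposes do not include doing so.

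A blank week is therefore ambiguous. An analysis plan can lay down how to score a blank, but it cannot recover whether the woman walked if nobody asked. What is at stake is the reading of a primary feasibility outcome: low measured adherence in the combined arm could reflect the exercise programme, the diary, or both. Log non-completion is also not named as a feasibility result, because item 3 of the Primary Outcome judges acceptability of data collection from gaps in the questionnaires.

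**Working it through.** **Inputs from the Protocol.** Programme length 8 weeks; exercise threshold two thirds (67%) of the duration; 20 women per arm; 10% to 15% missing data expected (Primary Outcome, item 2).

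**Assumptions not in the Protocol.** (a) An unlogged week is scored as not done. (b) Each exercised week is logged with probability q, independently of other weeks. No logging rate is given. The range q = 0.85 to 0.90 follows if the expected 10% to 15% missing data, which is not stated for logs, applied to log weeks. A wider range is shown.

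**Step 1: the threshold.** 2/3 = 66.7%, which rounds to the stated 67%. 8 × 2/3 = 5.33 weeks (8 × 0.67 = 5.36), so 6 whole weeks are needed, or 5 if rounded down.

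**Step 2: chance of being classed adherent.** For a woman who truly exercised enough in w weeks:

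P = P(Binomial(w, q) ≥ 6)

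- w = 8, q = 0.90: 0.9^8 + 8 × 0.9^7 × 0.1 + 28 × 0.9^6 × 0.1^2 = 0.430 + 0.383 + 0.149 = 0.962
- w = 8, q = 0.85: 0.272 + 0.385 + 0.238 = 0.895
- w = 6: all six weeks must be logged, so P = q^6, giving 0.531 at q = 0.90 and 0.377 at q = 0.85

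| q | w = 8 | w = 7 | w = 6 |
| --- | --- | --- | --- |
| 0.95 | 0.994 | 0.956 | 0.735 |
| 0.90 | 0.962 | 0.850 | 0.531 |
| 0.85 | 0.895 | 0.717 | 0.377 |
| 0.80 | 0.797 | 0.577 | 0.262 |
| 0.70 | 0.552 | 0.329 | 0.118 |

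For q = 0.90 to 0.85, the chance of being wrongly classed non-adherent is 3.8% to 10.5% (w = 8), 15% to 28% (w = 7) and 47% to 62% (w = 6).

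**Step 3: the softer threshold.** If 5 weeks suffice, the same chances fall to 0.5% to 2.1%, 2.6% to 7.4% and 11% to 22%.

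**Step 4: the arm.** If all 20 women truly met the 6-week threshold, the expected number classed adherent at q = 0.90 to 0.85 is 20 × 0.962 = 19.2 down to 17.9 when all exercised 8 weeks. It is 20 × 0.531 = 10.6 down to 7.5 when all exercised exactly 6.

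**Step 5: is exactly 6 weeks a remote case?** Suggested walking at its lower end is 10 × 2 = 20 minutes in weeks 1 and 2, 10 × 3 = 30 in weeks 3 to 5, 10 × 2 × 3 = 60 in weeks 6 and 7, and 90 in week 8. If only walking minutes count, since strength is logged in sets and repetitions, six weeks reach 30 minutes and there is no slack. Goals are set individually, so this illustrates that the case can arise; it does not predict how often.

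**The case against.** A reader might infer that an unlogged week counts as an unexercised one, that measured adherence is therefore biased downwards, and that adherent women will be misclassified. The Protocol does not support that.

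- **No zero-scoring rule.** Nothing says how a blank week is scored. The Statistical methods section speaks of imputation where outcomes are missing, and the scoring rule may stand in an analysis plan that is not at hand. Without assumption (a), the figures above have no force. This stands.
- **Direction unknown.** Self-completed logs can over-report as well as under-report, so the net error could go either way. This stands. That fatigued women log less is plausible but not documented.
- **Logging is supported.** There is a goal-setting diary, and Appendix 9 describes self-monitoring, text or e-mail prompts and feedback on completed goals. Such feedback suggests that the researcher will learn something of what was done. This makes poor logging less likely, but none of it is named as an adherence record.
- **The contrast with mindfulness is limited.** Weekly mindfulness sessions leave an app trace, but home practice is also entered by hand and only encouraged. It would be wrong to say that one component is measured automatically and the other is not.
- **Independence is a simplification.** If non-logging concentrates in a few women, the distribution across the arm changes.
- **No decision rule is tied to adherence.** No stop or proceed threshold is given, so nothing would automatically declare exercise infeasible. The focus groups cover data collection and the exercise component, which helps to separate the two burdens qualitatively, though not to classify individual women.

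These points limit the claim about consequences. They leave the gap in data collection untouched.

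**Conclusion.** The point holds as a gap in data collection, not as a demonstrated bias. Exercise minutes, which feed the first primary outcome, have one source: a manual log that is encouraged or asked for. The weekly contact is not named as a second source, so not logged and not done cannot be separated.

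The possible size is conditional on zero scoring, a 6-week threshold and independent logging at an assumed 0.85 to 0.90. It is small for women with weeks to spare and large for those at the threshold, where about half or more could be misclassified. Under other scoring rules, or with over-reporting, the size and even the sign may differ. The change is cheap and worth making before participants start the programme, because the information cannot be reliably recovered after the 8 weeks.

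**What to change.** At the existing weekly contact in the combined arm, have the researcher record the previous week's walking minutes and strength sessions, fill any gap in the log, and mark the week as done, not done or unknown. Add this purpose to the description of the contact and name it as a data source in item 1 of the Primary Outcome. Report exercise adherence from the combined record, with log-only adherence beside it. Report log completion separately as part of the acceptability of data collection.

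The cost is one or two questions in a contact already planned and a short record page. No additional contact is needed, and the exercise programme does not change. The downside is that recall given to the researcher who also sets the goals may be generous. Showing the log-only figure alongside makes the difference between the two sources visible.

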To explore the feasibility of conducting an 8- week online mindfulness and home-based walking and strength training programme for the management of cancer related fatigue in women with gynaecology cancer. The following objectives will assess feasibility outcomes:

1. To assess participant intervention adherence, study retention and attrition rate.
2. Explore the acceptability of using an online platform for the delivery and data collection of the exercise and mindfulness programme.
3. Explore the perspectives of participants concerning satisfaction (eg the intervention and its’ delivery) perceived value, barriers and facilitators of the online programme.

Secondary aim

To evaluate the effect of an 8 week exercise and mindfulness programme on cancer related fatigue as a primary clinical outcome and the effect on anxiety, depression, sleep and QoL as a secondary clinical outcome in an online setting.

Section 2 Methods

Study design

The study design and development have been reviewed and feedback considered from 2 patient and public involvement representatives.

This design will involve 2 parts firstly, an intervention part which is designed as an open, randomised, control trial with 1:1 allocation to either the mindfulness only group or the exercise and mindfulness group.

Following the intervention the second part will be online focus groups which will be conducted with participants once they have completed the intervention.

Study setting

Both parts of this study, intervention and focus groups, will be conducted online via a web-based, mobile application interface. Participants will be notified that data usage with this app will be minimal and battery usage of mobile devices may increase requiring additional charging of device. Therefore, participants should not incur any additional financial burden.

Participants & Eligibility

Eligibility criteria:

Inclusion criteria:

1. Women >18 years old and able to speak and read English.
2. Diagnosed with stage I-IV gynaecology cancer including endometrial, ovarian, cervical, vaginal, vulva, fallopian tube.
3. A minimum of 3 months post-treatment and up to 5 years.
4. Experiencing fatigue and at screening have a numerical rating score of $\geq$4 on a scale of 0-10.
5. Currently sedentary (exercising < once a week for 20 minutes at a vigorous intensity or, two times per week for 30 minutes at moderate intensity or < 20 minutes three times per week, for the past 6 months).

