6. Ambulatory and without the use of a walking aid.
7. Capacity to give informed consent.
8. Access to computer/tablet/smartphone.
9. Access to internet.

Exclusion criteria:

1. Currently actively and regularly practising mindfulness.
2. Have a confirmed diagnoses of Schizophrenia spectrum disorder, Bipolar disorder, Post-traumatic stress disorder, or risk factors for psychosis (eg personality disorder) as participation in a mindfulness program is contraindicated and maybe detrimental to well-being (Van Dam *et al.* 2018).
3. Have an existing medical condition that may inhibit safe participation in the exercise part of the intervention study.
4. Previously diagnosed with a fatigue-related co-morbid medical condition (i.e. Fibromyalgia, Chronic Fatigue Syndrome, Multiple Sclerosis (MS), Myalgic Encephalopathy (ME), Lupus or Arthritis)
5. Have no e-mail address.
6. Participating in other intervention trials.

Sample size

The sample size for this study is based upon feasibility and review of similar studies. The literature demonstrates that feasibility studies with similar interventions and methodologies within the cancer population recruit on average 40 participants in total (Eyles *et al.* 2015a; Victorson *et al.* 2017; Price-Blackshear *et al.* 2020). Therefore it is anticipated that this study will recruit a total of 40 participants with 20 in each arm of the study.

Procedure & Materials

Recruitment.

This study will adopt the approach of rolling recruitment and once participants have been screened and consented will commence the intervention they have been randomised to. Recruitment will take place through the following charities: Cancer Focus, Macmillan and Action Cancer. These organisations have agreed to contact their service users through social media (Facebook, Twitter, Instagram), leaflet drops and other service providers the organisation provide such as counsellors, clinical nurse specialist, support workers etc (appendix 1). They have also provided written confirmation of their commitment to assist in recruitment for this study (appendix 2).

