If participants are interested in the study they can self-refer and a contact number for the researcher will be made available through the leaflets, social media or service providers. Participants can call the researcher for further information and if willing and interested screening for eligibility will be performed by the researcher (appendix 3). Once this is complete and it is established that participants meet the criteria participants will be e-mailed participant information sheet by the researcher (appendix 4) and time given to read and ask any questions regarding this. Participants can contact the research team if they have any further questions. Consent (Appendix 5) will be obtained after participants have been given one week to consider the study. An Qualtrics link to an electronic version of the consent will be emailed to participants.

Randomisation

Participants will be randomly allocated to either group through 1:1 allocation. Participants will be randomly assigned using computer-generated random number tables. A researcher/statistician not involved in treatment delivery or collection of outcomes will generate the random allocation sequence. Concealment of treatment allocation will be by placing individual random assignments into serially numbered sealed envelopes and be held by researcher/statistician not involved in treatment or outcome measure collection.

Participants will be notified of which group they have been allocated to via the e-mail they have supplied. A member of the research team will e-mail the participant with this information.

Data collection methods

Outcome measures

Data collection for outcome measures will be self-report measures using valid and reliable tools for measuring these outcomes. Participants will be asked to complete these assessments following randomisation at baseline and on completion of the programme. At baseline participants will also complete demographic information such as age, cancer type, education, income, and education (appendix 6). All of this will be done via Qualtrics (appendix 7), an e-mail reminder will be sent 2 weeks after the initial invitation if completion has not occurred. Access to intervention will only happen once all baseline assessments have been completed.

The following self-report measures will be used to assess outcomes at baseline and post-intervention (copies and links to Qualtrics of all can be found in appendix 7).

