Group sizes can vary and can be between 4 and 12 for focus groups (Barbour 2008). For online focus groups, a more realistic number that has been suggested by the literature would be a maximum of 6 per group (Holloway 2005; Halliday *et al.* 2021). The number and size of groups will also be dependent on trial recruitment numbers and continue until data saturation, which will be reached when no new information is generated (Goei *et al.* 2020). Separate groups will take place for each intervention group to ensure that each group can share and reflect on their similar experience of the intervention they took part in.

Materials

Once participants have completed the 8 weeks of the intervention, they will be invited to take part in online focus groups. An e-mail invitation (Appendix 10) will be sent along with a participant information sheet (Appendix 11) about the focus group. A follow-up phone call will be made by the researcher. Interested participants will be sent a confirmation e-mail outlining a suitable time and date. Confirmation of attendance will be requested along with consent prior to the focus group taking part online. If consent (Appendix 12) has not been received before the focus group, it will still be possible to achieve consent on the day of the focus group. This will be achieved by allowing the participants to enter the online focus group on Microsoft Teams (MS Teams) into a separate room and the consent process will occur before allowing participants to be allowed into the main focus group. A semi-structured interview guide (Appendix 13) shaped by relevant literature was developed which contained open-ended questions that reflected the objectives of the study. Probes will be used to elicit additional information when required. As the groups progress, the prompts will be developed to ensure that the phenomenon is thoroughly explored.

Procedure

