Participants who agree to take part will be allocated to groups, these will be mixed groups of age, cancer type and stage but all participants will have completed the same intervention. To ensure that groups retain participants from the same intervention, participants will be asked by the research team through e-mail to provide the research team with information of which group they were randomised to. The allocation of groups will be made by the research team prior to focus groups taking place. If group numbers are too large, small or unevenly distributed then a decision within the research group will be reached regarding on reallocation of participants to groups. Groups will take place as close to the completion of the intervention as is practical. The groups will be facilitated by 3 researchers one of whom will be a facilitator and will ensure that the discussion stays on topic and equal time is shared amongst participants. The other will be responsible for technical support and will support participants during the session, record the session and take notes. The 3^rd^ researcher will be present in case any participant becomes distressed and will need to be removed from the focus group. If participation in these focus groups causes distress for any participants, a distress protocol (appendix 15) is in place to manage this. The PhD researcher, [name], has undertaken training with Ulster University on conducting focus groups but will be supported by [name] and team in undertaking these focus groups. Participants will be informed that the sessions will be recorded and if possible asked to keep audio and video on as this will aid the flow of conversation and will allow the facilitator to take field notes to capture both verbal and non-verbal communication. All focus group discussion will be audio and video recorded, then transcribed verbatim for analysis (Barbour 2008)

Analysis of data from focus groups will be done using Thematic Analysis. This type of analysis is flexible and allows for the in-depth identification and interpretation of themes. (Holloway and Galvin 2016; Castleberry and Nolen 2018) The phases of the analysis will include: familiarising with data, generating initial codes, searching for themes, reviewing themes, defining and naming themes and integrating these themes into a final report for publication (Braun and Clarke 2006).

Secondary Outcomes

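### Programme acceptability is explored only among women who completed the intervention, so its themes may lean favourable; the follow-up questionnaires also lack a fixed date

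*Protocol*

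**What the plan says.** All references are to the Protocol.

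- **Study design** describes the second part of the study as "online focus groups which will be conducted with participants once they have completed the intervention".
- **Focus groups, Materials:** "Once participants have completed the 8 weeks of the intervention, they will be invited to take part in online focus groups".
- **Focus groups, Procedure:** "these will be mixed groups of age, cancer type and stage but all participants will have completed the same intervention".
- **Primary Outcome, preamble:** "These outcomes will assess participants that have completed or take part in the intervention part of the study". Item 4 then names focus groups as the means of assessing programme acceptability. Item 3 seeks reasons for dropping out, but only where they can be obtained.
- **Primary Aim, Objective 3** covers satisfaction, perceived value, barriers and facilitators.
- **Primary Outcome, item 2** expects that "the attrition rate will be approximately 20% with 10% to 15% of missing data".
- **Data collection methods, Outcome measures:** "Participants will be asked to complete these assessments following randomisation at baseline and on completion of the programme". The same section also refers to the second assessment simply as post-intervention, and Appendix 14 places it in the close-out column with no week attached.
- **Statistical methods** calls the primary analyses intention to treat on all data, with imputation of missing outcomes.

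**The concern.** Acceptability is a primary outcome, and its one stated source is a group of women selected by having completed the programme. A woman who stopped because the app, the time demand or the exercise did not suit her holds the information that Objective 3 asks for, yet she falls outside the invitation rule. The themes on barriers and acceptability would then come from those for whom the barriers could be overcome. A feasibility trial uses such themes to decide what to change before a larger study, and views not collected at the time are hard to recover later.

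The questionnaires raise a related but smaller matter. Their due date is expressed through completion of a programme that each woman works through in her own time. A woman who stops or falls behind has no clear date on which her forms are due, and nothing in the text says that she is still asked. An intention-to-treat analysis needs that to be settled.

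**Working it through.** **Inputs.** Planned size is 40, with 20 per arm (Sample size: "Therefore it is anticipated that this study will recruit a total of 40 participants with 20 in each arm of the study"). Allocation is 1:1 (Randomisation). Expected attrition is about 20%, with 10% to 15% missing data (Primary Outcome, item 2). The sample size has no power calculation behind it, so there is no derived figure to reproduce; the 20% is a stated expectation.

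**Step 1: who is invited.** Study design, Materials and Procedure all use completion of the intervention as the condition. The clause in Procedure is mainly about keeping the arms apart, but it assumes the same condition. The Primary Outcome preamble is wider, because it includes women who take part without completing. The two do not agree.

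**Step 2: whether women who stop have another route.** Attrition and retention count them. App data and logs record their engagement. Missing questionnaire items inform the acceptability of data collection. Weekly researcher contact looks for problems, and the distress protocol in Appendix b provides assessment, signposting and a follow-up call. Dropout reasons are sought where possible. None of these asks for views on content, delivery or barriers in the way Appendix 13 does.

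**Step 3: how many women.**

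- Not invited: 0.20 × 40 = 8, or 0.20 × 20 = 4 per arm.
- Invited: 40 − 8 = 32, or 16 per arm.
- If true attrition is 20% and women drop out independently, the central 95% binomial range is 3 to 13 of 40.

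**Step 4: how firm the 8 is.** It equates attrition with not completing. The protocol's adherence standard asks for 4 of the 8 mindfulness weeks and about 0.67 × 8 = 5.4 weeks of exercise, so a woman can be adherent without having finished 8 weeks. If completion means every module, more than 8 could be excluded. If it means reaching week 8, poorly engaged women are included and the number could be lower.

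**Step 5: effect on the findings.** Procedure specifies thematic analysis, so there is no acceptability percentage or threshold to which a bias in points could be attached. Only the likely direction can be argued.

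**Step 6: questionnaire timing.** The outcome section gives two descriptions, on completion and post-intervention. Appendix 14 gives close-out without a week. The description of the mindfulness intervention calls the app asynchronous, and completing each module before moving on is only encouraged. The Primary Outcome section does fix an 8-week length. Together these leave the date open, but they do not exclude anyone.

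For scale, complete follow-up would be 32 × 0.90 = 28.8 to 32 × 0.85 = 27.2 women if the missing data fall among the 32. It would be 40 × (1 − 0.20 − 0.10) = 28 to 40 × (1 − 0.20 − 0.15) = 26 if they are added to attrition. The protocol does not say which applies.

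**The case against.** The best defence has four parts.

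1. **Women who stop are not ignored.** Step 2 lists what is collected, and Appendix 13 asks completers about barriers, dislikes and improvements. This stands against any reading that stoppers are left out of the trial. It does not supply their views on the programme.
2. **The bias is not shown.** A reader might infer that the trial will report acceptability too high by some number of points. The documents do not support this: no such percentage is planned, and if women who stop think as completers do, there is no bias. What stands is a plausible direction.
3. **The questionnaires are not withheld.** A reader might infer that stopping the app means no follow-up form, so that stopping becomes missing data by design. No text says so. Completion can mean the end of the 8-week period, the post-intervention wording carries no completion condition, weekly goal setting implies a calendar, and the analysis is intention to treat on all data. Nor can it be said that all 8 women's forms could still be collected, because attrition is not defined as stopping the app while remaining contactable. What stands is that the time point is not fixed.
4. **Mixed groups may not suit.** Separate groups are planned so that women can share a similar experience, and a woman who stopped early may not fit. This is fair, and is a reason to offer an alternative to the group.

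The invitation, information sheets and consent forms are not available here and may say more about women who stop. The protocol's own wording would still need to agree with them.

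**Conclusion.** The point holds for the focus groups. Under the rule as written, the only stated measure of programme acceptability reaches completers only, in conflict with the Primary Outcome preamble and at odds with Objective 3. At the protocol's expected attrition, about 8 of 40 women (4 per arm) would not be invited, on the assumption that attrition and non-completion coincide. The acceptability and barrier themes may be biased favourably, by an amount that cannot be computed. For the questionnaires the conclusion is narrower: the date is unfixed and coverage of women who stop is unstated. The change is worth making because it concerns a primary outcome and is cheap.

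**What to change.** - **Study design, and focus groups Materials and Procedure:** invite every randomised woman who has not withdrawn consent to contact, 8 weeks after she receives app access, whatever her progress. Assign her to her own arm's group. If a woman who stopped does not join, offer her the Appendix 13 questions by e-mail or on the follow-up call that Materials already plans.
- **Data collection methods and Appendix 14:** state that the post-intervention questionnaires go to all randomised women 8 weeks from app access, regardless of progress, and put that week in the Appendix 14 table.
- **Starting point:** access is given only after the baseline forms are complete, so name a fallback date for a randomised woman who never receives it.

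The cost is protocol, invitation and information-sheet wording and a handful of e-mails or calls. No part of either intervention changes. The downside is that uptake among women who stopped is likely to be modest, so the number invited and the number responding should be reported separately for them.
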